
Use of health services by patients in the PCMR will also be documented with medical administrative data (medical services, hospitalizations, emergency room visits), using the patient's health insurance number to match medical administrative data to data from the regional computerized registry on chronic illnesses and to his or her survey data.

Regression models will be built to assess the program's effects on patients, in terms of biological parameters, lifestyle habits, health services utilization, chronic illness follow-up, self-management, quality of life and care experience, based on the CSSS, degree of exposure to the program, patient characteristics, and organizational characteristics of primary care clinics where patients are seen. Particular attention will be paid to patients' sociodemographic characteristics (male/female, age, income, education) in terms of equity of access to services. Linear models will be constructed for continuous dependent variables (e.g. before-after intervention differences in HbA1c or BP). Logistic models will be used for dichotomous dependent variables (e.g. clinical targets achieved or not by the end of the intervention, dichotomized indices). Longitudinal analyses will enable us to model the evolution of dependent variables throughout the follow-up period. These analyses will be performed using multilevel models (Generalized Linear Mixed Models) [41] in which individual repeated observations will be nested within patients. We will thus be able to control for certain fixed subject characteristics as well as for time-varying covariates.

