#### Patient recruitment and power calculation

We plan on recruiting about 250 patients a year in each participating CSSS, for a total of 3500 patients over 28 months. Assuming that recruitment rate is constant, we estimate that the 2000 patients recruited in the first 16 months could be the object, during the study, of at least three observations for data collected using questionnaires, and at least six observations for clinical data (Table 1). For the 1500 patients recruited during the last 12 months of recruitment, we will have two observations for data collected using questionnaires and at least four observations for clinical data. We expect that an initial sample of 3500 subjects, with an attrition rate of 20%, would ensure 2800 subjects available for analyses over two time measures. This sample size would allow detection of a difference in average between two territories that is about 0.14 in standard deviation units in longitudinal linear models, and about 7%, with a power of 80% at the 0.05 significance level in logistic models [42,43]. These calculations are conservatively based on the number of subjects measured twice; use of effective covariables or of a higher number of observations per subject should lead to an increase in the power of models.

**Table 1 T1:** Patient recruitment and numbers of data collected

Number of patients	Questionnaires (services utilization, affiliation to primary care physician, chronic illness monitoring, self-management, quality of life)	**Registry ****data ****(biological measures and lifestyle habits)**
500 patients recruited in first 4 months	0, 12, 24 and 36 months	0, 3, 6, 12, 18 and 24 months

500 patients recruited in months 5 to 8	0, 12 and 24 months	0, 3, 6, 12, 18 and 24 months

500 patients recruited in months 9 to 12	0, 12 and 24 months	0, 3, 6, 12, 18 and 24 months

500 patients recruited in months 13 to 16	0, 12 and 24 months	0, 3, 6, 12, 18 and 24 months

500 patients recruited in months 17 to 20	0 and 12 months	0, 3, 6, 12 and 18 months

500 patients recruited in months 21 to 24	0 and 12 months	0, 3, 6 and 12 months

500 patients recruited in months 25 to 28	0 and 12 months	0, 3, 6 and 12 months

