Data will be collected in three phases, as per the program implementation stages. Semi-structured interviews with individuals from the ASSS and CSSS responsible for program implementation are scheduled for the beginning of the project (start-up phase). They will provide an initial portrait of regional services organization related to the activities of the program being implemented and will document the program components (objectives and purposes, roles and actors involved, resources and activities). They will also be used to define the dynamics in each implementation site. Interviews with respondents from each territory will focus on local historical contexts of interventions with people at risk of or who have diabetes or hypertension; organizational contexts of the CSSS; PCMR activities already in place and their components; local resources allocated; number of medical clinics and physicians involved; and number of patients targeted by the program. A second and third round of semi-structured interviews with local and regional respondents will be conducted 20 and 40 months after the beginning of the program. They will document PCMR activities actually implemented and degree of program implementation, activities set up to integrate the PCMR into the CSSS's regular activities, and obstacles and facilitators encountered. The questionnaires for physicians will also document barriers and facilitators. These contextual determinants will be grouped by dimension and conveyed with descriptive variables. The interview grids used at the beginning of the implementation of the project are included in Additional files 7a and 7b. Data collection tools that will be used 20 and 40 months after the beginning of the program will be constructed after analysis of the data collected at the beginning of the implementation of the project.

Based on the information collected throughout the project, a descriptive analysis of each case (implementation setting) will be performed. Six monographs, one for each setting, will describe the phases of PCMR implementation and its explanatory factors.

#### Objective 3

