Two approaches will be used to attain this objective. The first is designed to complement the analysis proposed in Objective 2. Using the material compiled in the monographs, quantitative variables and categorical taxonomic variables will be created and integrated into regression analyses explaining the effects of the program. Regression models will be built to assess the influence of the variables pertaining to PCMR set up and implementation in the various CSSS on the effects observed among patients, controlling for degree of exposure to PCMR, patient characteristics and the characteristics of primary care clinics where they are seen. Given the low number of upper level units (6 CSSS), variables linked to CSSS will be considered as fixed effects in regression models. Linear regressions will be constructed for continuous dependent variables, while logistic models will be used for dichotomous dependent variables and multilevel longitudinal models for dependent variables that are the object of repeated measures. A similar analysis strategy will be used to assess the influence on medical practice of variables that reflect PCMR set up and implementation in various CSSS.

The second approach will be interpretive: from the material used to produce the monographs, participants' statements on the relationship between program effects and components will be noted and analyzed. Conclusions drawn from these two approaches will be validated in discussion groups.

#### Objective 4

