### Strengths and limitations of the proposed project

Our project has both strengths and weaknesses. Strictly speaking, for a comparative analysis, the number of CSSS in our study is relatively small. However, for a multiple case analysis strategy, this number is sufficient to show contrasts and can rather be seen as a strength of our study. The absence of a control group is a limitation but in this type of study, it is impossible to use an experimental design; we replaced it with a quasi-experimental design [47] and a hybrid analysis strategy that combines quantitative and qualitative aspects. Triangulation increases internal but also external validity, which is often lacking in experimental designs. Moreover, although the 40-month observation period is long enough to show the effects of the PCMR and to document the implementation process, it may not be sufficient to estimate, over the longer term, the sustainability of the effects and of activities undertaken.

Some of the strong points of our study include the fact that it will enable us to fill certain gaps in knowledge and, more particularly, to evaluate the application of the CCM to a primary care "case management" approach rather than to "disease management". It will also allow us to evaluate CCM implementation from a systemic perspective based on the will of the ASSSM to completely implement the proposed program in all Montréal CSSS. Mostly, our study will identify the contextual factors that can modulate the effects of the CCM and that can be associated with successful implementation and with the effectiveness of such a program. These contextual elements will enable us to extrapolate our results to other contexts with similar conditions as well as to other chronic illnesses. The study will also allow us to assess the impact of implementing a program inspired from the CCM on consolidation of local services networks. Finally, in terms of the methodology, we should add that other strengths of the project are sample size, repeated number of observations and use of numerous tools (questionnaires) that have either been validated or used in our previous studies.

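### Objective 3 tests implementation and context variables that are constant within a CSSS against patient-level error, so their standard errors are too small if any other difference between the six territories remains

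*Protocol article*

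**What the plan says.** All references are to the protocol article, under Methods/Design unless stated.

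- **Source of the variables (Objective 2 and Objective 3).** Interviews take place at start-up and at 20 and 40 months. From them, "Six monographs, one for each setting, will describe the phases of PCMR implementation and its explanatory factors". Objective 3 continues: "Using the material compiled in the monographs, quantitative variables and categorical taxonomic variables will be created and integrated into regression analyses".
- **Outcome and adjustment (Objective 3).** The models assess the influence of these variables "on the effects observed among patients, controlling for degree of exposure to PCMR, patient characteristics" and the characteristics of the primary care clinics.
- **Treatment of the CSSS level (Objective 3).** "Given the low number of upper level units (6 CSSS), variables linked to CSSS will be considered as fixed effects in regression models".
- **Error structure.** The models named are linear, logistic and multilevel longitudinal. The only nesting described is in Objective 1: mixed models "in which individual repeated observations will be nested within patients".
- **Numbers (Patient recruitment and power calculation).** The recruitment target reads: "We plan on recruiting about 250 patients a year in each participating CSSS, for a total of 3500 patients over 28 months". With 20% attrition, 2800 remain for analysis.
- **Limitations (Strengths and limitations).** The authors concede that "for a comparative analysis, the number of CSSS in our study is relatively small", and add that six is enough to show contrasts in a multiple case analysis. Objective 3 also has a second, interpretive approach, and conclusions from both are to be validated in discussion groups.

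**The concern.** A variable scored once per territory has six values, however many patients are recruited. Evidence on whether it explains outcomes comes from how the six territories line up, and the relevant noise is how much territories differ for all other reasons. A regression whose only error terms are the patient and the observation within patient has no place for that noise. It attributes the leftover territory differences to the implementation variable, and it computes the standard error as if each patient were a separate test of it.

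The stated rationale does not help. Few upper-level units is a good reason to doubt an estimated CSSS variance, but giving the CSSS-level variables fixed coefficients does not supply the missing error. The naive test is valid only if no residual between-CSSS variance remains. The article leads one to expect some: Objective 1 anticipates that effects will vary by setting, and the Design section expects the program to adapt to each CSSS.

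At stake is the claim, in the Abstract and again in Strengths and limitations, that the study will identify contextual factors linked to effectiveness and allow extrapolation to similar contexts.

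**Working it through.** **Inputs from the article.** 6 CSSS; 250 patients per CSSS per year; 28 months; 20% attrition; significance level 0.05 (taken as two-sided). **Assumed, because the article gives no figure:** residual between-CSSS ICC from 0 to 0.05.

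**1. The plan's own figures.**
- Recruitment: 250 × 6 × 28/12 = 3500. Analysed: 3500 × 0.8 = 2800. Per CSSS: 2800/6 ≈ 467.
- The detectable difference of 0.14 SD at 80% power reproduces as one territory against the other five with independent patients: (1.96 + 0.842) × √(1/467 + 1/2333) = 0.142.
- Two single territories (467 v 467) give 0.183 by the same formula. That reaches 0.14 only with an unstated baseline correlation of about 0.65 (ANCOVA) or 0.71 (change score). Nothing below rests on which reading was meant.
- Patient-level error is legitimate for comparing named territories. It stops being enough when the difference is attributed to an implementation or context score.

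**2. Variance actually present against variance assumed.** Take a 3 v 3 contrast of CSSS, with outcome SD 1 and m = 467.
- True variance: (2/3) × [ICC + (1 − ICC)/m].
- Variance used by the patient-level model: (2/3) × (1/m).
- Ratio: DEFF = 1 + (m − 1) × ICC = 1 + 466 × ICC.

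**3. Rejection rate under the null.** 2 × [1 − Φ(1.96/√DEFF)]; effective sample size 2800/DEFF.

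| Assumed residual ICC | DEFF | Rejection at nominal 5% | Effective n |
|---|---|---|---|
| 0 | 1.00 | 5.0% | 2800 |
| 0.001 | 1.47 | 10.5% | 1910 |
| 0.002 | 1.93 | 15.9% | 1449 |
| 0.005 | 3.33 | 28.3% | 841 |
| 0.01 | 5.66 | 41.0% | 495 |
| 0.02 | 10.32 | 54.2% | 271 |
| 0.05 | 24.30 | 69.1% | 115 |

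Simulation (20,000 runs per ICC, six CSSS of 467, a 3 v 3 factor and a continuous score, no covariates) gave 4.8–5.0%, 10.5–10.6%, 28.3%, 40.8–41.4%, 53.8–54.8% and 69.1–69.7% at ICC 0, 0.001, 0.005, 0.01, 0.02 and 0.05.

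**4. An illustrative anchor.** If a typical pair of territories differed by the plan's 0.14 SD for reasons outside the model, the between-CSSS variance would be 0.14²/2 = 0.0098. Then DEFF = 1 + 466 × 0.0098 = 5.57, and the rejection rate is about 41%. The 0.14 is a design figure, not an estimate of residual variation.

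**5. Test at CSSS level.** In the same simulations, a regression on the six CSSS means with t on 4 df rejected 4.6–5.3% of the time at every ICC tried. The correlation needed for p<0.05 is 2.776/√(4 + 2.776²) = 0.811.

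**6. If CSSS indicators are also in the model.** Six indicators plus one time-constant CSSS variable make seven columns of rank 6, so that variable's coefficient is not estimable.

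**The case against.** - **The ICC is unknown and may be small.** The models adjust for exposure, patient and clinic characteristics. For continuous outcomes, before-after differences remove stable level differences between territories. What counts is the residual ICC of the change, and the article does not give it. This stands. A reader might infer that false-positive rates of 28–55% are a property of the plan, but that range corresponds only to an assumed ICC of about 0.005 to 0.02.
- **Not every variable has six values.** Implementation is documented again at 20 and 40 months, recruitment is staggered, and physicians' questionnaires also record barriers and facilitators. Some variables may therefore vary over time or within a CSSS. This stands too: the six-unit argument covers only variables constant within a CSSS. A reader might infer that no CSSS-linked variable could be estimated. Objective 3 does not list CSSS indicators among its adjustments, so the collinearity arises only if they are added, and then only for time-constant variables.
- **Objective 3 is not regression alone.** A reader might infer that it rests wholly on these p-values. The article pairs the regressions with an interpretive analysis, triangulates the two, validates the conclusions in discussion groups and admits the small number of CSSS. That lowers reliance on the regressions, but none of it changes their error term or limits what may be inferred from them.
- **Detail may sit in a fuller plan.** Multiplicity handling and standard-error corrections are fairly left there, and their absence is not held against the article. The fixed-effects choice and its reason, however, are stated here.

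**Conclusion.** The point holds for implementation and context variables that are constant within a CSSS. As described, their regressions carry no between-CSSS error, so they treat about 2800 patients as independent evidence on a six-unit comparison. Any residual difference between territories makes the tests anti-conservative.

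The size depends on an ICC that the documents do not give: from no inflation at 0, through 16% at 0.002 and 41% at 0.01, to about 69% at 0.05, for a nominal 5% test. These figures assume equal CSSS sizes of about 467, normal errors and no covariates beyond what the residual ICC absorbs. The figure of 2800 applies to patient outcomes; the physician models follow a similar strategy, but their number is not stated.

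The documents do not support an unconditional error rate, or a conclusion that Objective 3 as a whole fails.

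**What to change.** Replace the fixed-effects sentence in Objective 3 with a rule that sets the unit of inference:

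1. **Time-constant CSSS-level variables.** Estimate the case-mix-adjusted effect with its confidence interval in each CSSS. Then relate the six estimates to a pre-named implementation score, by t on 4 df or by exact permutation over the 6! = 720 orderings. Permutation suits a score with distinct values. A 3 v 3 category has only 20 allocations (6!/(3! × 3!)), so its smallest two-sided p is 2/20 = 0.10.
2. **Other contextual variables.** Present them descriptively, as input to the case-study comparison.
3. **Implementation scored repeatedly (20 and 40 months).** Use within-CSSS change, with inference on CSSS-periods rather than patients.
4. **CSSS indicators.** State whether they enter the Objective 3 models. If they do, time-constant CSSS variables must be left out.

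**Cost.** Analysis wording only; the data are the same. Power is limited: with six units |r| must exceed about 0.81 for p<0.05. For a 3 v 3 contrast tested on 4 df, the detectable difference at 80% power is 0.14 SD at ICC 0, 0.26 at 0.005, 0.34 at 0.01, 0.46 at 0.02 and 0.70 at 0.05. Most CSSS-level associations would be labelled exploratory, which fits the article's own remark that six territories suit a multiple case analysis better than a comparative one.

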### Ethical considerations

The project has received approval from the ASSSM's research ethics committee.

### Strengths and limitations of the proposed project

Our project has both strengths and weaknesses. Strictly speaking, for a comparative analysis, the number of CSSS in our study is relatively small. However, for a multiple case analysis strategy, this number is sufficient to show contrasts and can rather be seen as a strength of our study. The absence of a control group is a limitation but in this type of study, it is impossible to use an experimental design; we replaced it with a quasi-experimental design [47] and a hybrid analysis strategy that combines quantitative and qualitative aspects. Triangulation increases internal but also external validity, which is often lacking in experimental designs. Moreover, although the 40-month observation period is long enough to show the effects of the PCMR and to document the implementation process, it may not be sufficient to estimate, over the longer term, the sustainability of the effects and of activities undertaken.

Some of the strong points of our study include the fact that it will enable us to fill certain gaps in knowledge and, more particularly, to evaluate the application of the CCM to a primary care "case management" approach rather than to "disease management". It will also allow us to evaluate CCM implementation from a systemic perspective based on the will of the ASSSM to completely implement the proposed program in all Montréal CSSS. Mostly, our study will identify the contextual factors that can modulate the effects of the CCM and that can be associated with successful implementation and with the effectiveness of such a program. These contextual elements will enable us to extrapolate our results to other contexts with similar conditions as well as to other chronic illnesses. The study will also allow us to assess the impact of implementing a program inspired from the CCM on consolidation of local services networks. Finally, in terms of the methodology, we should add that other strengths of the project are sample size, repeated number of observations and use of numerous tools (questionnaires) that have either been validated or used in our previous studies.

### Knowledge translation and exchange plan, and partnerships

Since this project involves decision makers, clinicians and researchers, the knowledge translation and exchange plan is built into the study and consists in having mutual exchanges throughout the duration of the study. This close proximity fosters knowledge exchange and appropriation. The evaluation project is formative and many knowledge transfer activities are planned throughout the study.

To actualize some of these knowledge transfer activities, two regional steering committees (a select committee composed of regional decision-making/management/clinical representatives for which four or five meetings a year are planned, and a broader committee including local representatives that will meet twice a year) will be set up to support the research team during various stages of the project. Moreover, local coordination and clinical committees will be potential sources of information to document the degree of implementation and of venues to engage in dialogue to validate and interpret the results obtained. Halfway through the project, we will organize a meeting of local and regional decision-makers, managers and clinicians, who will be asked to react to results regarding the degree of program implementation in various CSSS and identification of factors that facilitate or hamper implementation.

We will also set up an advisory committee composed of representatives from among the project researchers and decision makers as well as other nationally and internationally known researchers and decision makers (some from other provinces) with expertise in research on primary care services organization and chronic illnesses. We plan to have two meetings with this committee to help us focus data collection and result analyses to promote the project's specific contribution to current knowledge and increase the potential to adapt our results to other contexts.

At the end of the project and with the help of the Institut national de santé publique du Québec (INSPQ), we will set up an exchange forum that will allow us to add more decision makers and researchers to the advisory committee; they will enhance adaptation of research results in the contexts of Québec and of other Canadian provinces, as well as internationally. The forum will present an opportunity to set up a more permanent structure for collaboration among researchers and decision makers, and thus enhance the outcome and value of our research by developing prolonged and sustainable partnerships. Our team has proved its capacity to implement such a structure. The exchange forum will bring together decision makers from the areas of primary care services organization and chronic diseases (from clinics, and local and provincial decision makers) as well as researchers from various backgrounds with whom the research team has collaborated for several years.

Moreover, we will benefit from the network the INSPQ developed through the Initiative sur le partage des connaissances et le développement des compétences, a consortium of provincial, regional and local partners (including CSSS) whose mandate is to implement population-based responsibility. Results will also be presented at conferences in Québec (e.g. Journées annuelles de santé publique, Rendez-vous de la gestion des maladies chroniques) as well as at national and international meetings. A research report will be written and scientific articles submitted for publication.
